### Sample size

The sample size is estimated at 4356 participants in total and is calculated on the basis of the following assumptions: 1:1 randomization, two-sided significance level of 0.05, power of 0.9, intra-cluster correlation coefficient of 0.01; and with an average of 1.5 citizens in each household, we calculated the design effect [33] to be 1.05. Calculations are further based on the objective of being able to detect a difference of 5 percentage points in effect size based on an attendance rate of 53–58%. The investigators determined this 5 percentage point difference to be clinically meaningful based on expert opinion [7–9, 34] and based on the run-in period where the participation rate was 53%. Also, an increase of 5 percentage points would deliver clinically meaningful benefit if scaled in a nationwide program. In order to reflect a possible clustering effect of the general practitioners (*n* = 46), which seldom exceeds 0.01 in primary care settings [35], the intra-cluster correlation coefficient was included. To limit the missing data in our study [36], incomplete questionnaires and incomplete spirometry measurements will be excluded. Non-attendees will be described with information supplied from national registers [21, 22]. A sensitivity analysis will also be performed.

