### The intervention

The intervention group (*n* = 2178) receives a modified invitation and a leaflet which highlights the benefits of spirometry as part of a health check and provides information about how to prevent lung diseases. The invitation was developed in collaboration with the Danish Lung Association and was tested for content and comprehensibility on a focus group before dispatch of the invitations to the intervention group. The citizens are recommended to visit the homepage for further information and advice on how to prevent lung diseases [32]. All the material can be accessed in Additional file 3.

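### The design effect of 1.05 does not follow from the stated ICC of 0.01 and 1.5 citizens per household, which give 1.005, and the total of 4,356 was built on 1.05

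*Protocol article*

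**What the plan says.** The Sample size section states the result as "The sample size is estimated at 4356 participants in total". The inputs are "1:1 randomization, two-sided significance level of 0.05, power of 0.9", and the aim is to "detect a difference of 5 percentage points in effect size based on an attendance rate of 53–58" percent. For clustering it gives an "intra-cluster correlation coefficient of 0.01; and with an average of 1.5 citizens in each household, we calculated the design effect", and the value reported is 1.05.

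Later in the same section the ICC is explained as an allowance for clustering by general practitioner (46 of them), a quantity "which seldom exceeds 0.01 in primary care settings". No ICC for households is given. The Randomization section makes the household the unit of randomization. The sections on the routine invitation and on the intervention each give 2,178 citizens per group.

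**The concern.** One sentence prints two inputs and a result said to be calculated from them, and the result does not follow. The ICC is the only clustering assumption in the sample size of a household-randomized trial. As printed, a reader cannot tell whether the 90% power rests on an ICC of 0.01 or on a larger one.

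The source of the 0.01 adds to the doubt. It is argued from correlation among patients of the same practice, but the cluster size beside it is that of a household. These are different clusters and there is no reason for their ICCs to agree. The article itself expects household members to influence one another: under Strengths and limitations it gives shared motivation as the reason for randomizing whole households.

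**Working it through.** **Inputs** (all from Sample size unless noted): attendance 0.53 v 0.58; two-sided alpha 0.05; power 0.90; 1:1 allocation; ICC 0.01; mean household size 1.5; stated design effect 1.05; stated total 4,356; 2,178 per arm (sections on the invitation and the intervention); 46 general practitioners.

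**Step 1. Reproduce the plan's total.** For two proportions with pooled variance under the null and no continuity correction:

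n per arm = [1.960 × √(2 × 0.555 × 0.445) + 1.282 × √(0.53 × 0.47 + 0.58 × 0.42)]² / 0.05² = 2,073.98, so 2,074.

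- 2,074 × 1.05 = 2,177.7, so 2,178 per arm and 4,356 in total. This matches exactly.
- The unpooled formula with 1.05 gives 4,350, and the continuity-corrected formula with 1.005 gives 4,250. Neither matches.

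So 1.05 was the multiplier used; it is not just a misprint of 1.005.

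**Step 2. Recompute the design effect.** With DE = 1 + (m − 1) × ICC:

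- Stated inputs: 1 + 0.5 × 0.01 = 1.005.
- ICC needed for 1.05 at m = 1.5: 0.05 / 0.5 = 0.10.
- Mean cluster size needed for 1.05 at ICC 0.01: 1 + 0.05 / 0.01 = 6.
- Unequal household sizes, assuming half singles and half pairs: the size-weighted mean is (0.5 × 1 + 0.5 × 4) / 1.5 = 1.667, so DE = 1 + 0.667 × 0.01, about 1.007.
- Practices as clusters: 4,356 / 46 = 94.7 citizens each, so DE = 1 + 93.7 × 0.01, about 1.94.

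None of these readings gives 1.05 from an ICC of 0.01.

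**Step 3. Consequence on the stated inputs.** 2,074 × 1.005 = 2,084.4, so 2,085 per arm and 4,170 in total. That is 4,356 − 4,170 = 186 fewer citizens (4.3%). Power at 4,356, using 2,178 / DE as the effective size per arm, is 91.2% with 1.005 and 90.0% with 1.05.

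**Step 4. Sensitivity to the undocumented household ICC.** The ICC values below, apart from 0.01, are assumptions and not figures from the article.

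| Household ICC | Design effect | Power at 4,356 |
|---|---|---|
| 0.01 | 1.005 | 91.2% |
| 0.1 | 1.05 | 90.0% |
| 0.3 | 1.15 | 87.2% |
| 0.5 | 1.25 | 84.4% |

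**The case against.** The best defence is that little turns on this. Alpha, power, the two attendance rates, the design effect of 1.05, the 2,178 per arm and the total all agree with one another; only the step from ICC and household size to the design effect fails. If 0.01 is right, the trial is slightly larger than it needed to be and keeps its power. About 3,500 participants had been enrolled when the article was submitted, so the point cannot reshape the design. All of this stands and limits the severity. It does not make the printed calculation correct.

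A reader might infer more than the article supports, in four ways.

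- *The inflation for clustering is overstated tenfold (5% against 0.5%).* This is true only if 0.01 is the intended ICC. If the ICC is the misprint, nothing is overstated.
- *The ICC was really 0.10.* That value reproduces the total, but it appears nowhere in the article, and the reason given for 0.01 would contradict it. Picking an ICC because it returns the sample size is not a justification.
- *The total cannot be reproduced.* It can, exactly, from 1.05.
- *The trial is underpowered, for example because of the value near 1.94 with practices as clusters.* Practices are not the randomized units, so that figure shows only that this reading does not yield 1.05. Lower power from a larger household ICC is possible, but it rests on assumed values.

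**Conclusion.** The point holds in a limited form. An ICC of 0.01 and 1.5 citizens per household give a design effect of 1.005, while 1.05 is stated and was used to reach 4,356. Taken at the stated ICC, the error is on the safe side: 186 citizens more than required and a little over one percentage point of extra power. The article does not show which of the two numbers is the slip.

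The safe direction depends on 0.01 being an acceptable value for households, and the article supports it only at practice level. Within the assumed range of 0.1 to 0.5, power at 4,356 runs from 90% down to 84%. The size rests on the standard design-effect formula and the uncorrected pooled test, which the exact match in step 1 supports. It is a moderate correction of a stated figure and gives no ground for changing enrolment.

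**What to change.** Go back to the original calculation, find which value was used and where it came from, and restate ICC, cluster level, design effect, total and power as one consistent set:

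- If the ICC of 0.01 is kept, give the design effect as 1.005, the requirement as 4,170, and power of about 91% at 4,356. Explain why a practice-level value is taken for households.
- If the design effect of 1.05 is kept, state a household ICC of 0.10 and give a source for it. Separate it from the sentence on general-practice clustering, which cannot serve as its support.

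Either way, name the cluster that the ICC describes, and add a line with power at 4,356 over an assumed range of household ICCs, labelled as assumed, such as the one in the working.

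The cost is a few corrected sentences in the Sample size section. The registry entry and the statistical analysis plan were not available, so check whether they carry the same figures and correct them only if they do.

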### Randomization

Randomization is performed on clusters defined by households based on addresses from the Danish Civil Register [21, 22]. Furthermore, the randomization is balanced at the general practitioner (GP) level to ensure distribution of the follow-up workload over 5 years. Using the same index individual per households, 4356 citizens randomized to group 4 in the CHPP are further randomized by household into two parallel groups: intervention or comparison (Fig. 1). Randomization is handled by an independent statistician. Implementation and booking are handled by a data manager. The intervention, the outcome, and the group assignment are not revealed to the participants, And the health care professionals also remain blinded. The blinding will be unlocked as the last spirometry measurement is done in December 2016.

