### Strengths and limitations

Participants will be enrolled directly from the general population; therefore, they will not receive any screening prior to inclusion. Thus, the generalizability will not only reflect certain at-risk populations such as current smokers, prior smokers, or citizens with chronic disease. The high transferability of the invitation material and the application of the intention-to-treat principle provide a high external validity. Moreover, the objective measure of attendance contributes with a high internal validity. We chose cluster randomization by household to limit the expected contamination between attendees living together, because motivation to attend a health check will potentially impact the entire household. To avoid having attendees refuse to participate, households are invited together and two reminders are sent out. Furthermore, appointments are scheduled outside of work hours. Finally, we have the unique opportunity to use the Danish registers as a population-based health care database with information about the non-attendees [21].

The present study has some limitations. Firstly, we are aware that both groups have the same accessibility to the webpage regarding how to prevent lung disease, and this may dilute the difference between the two groups. Secondly, the right level of extra information is difficult to achieve. Too much information may cause the participants to believe that the study is only about lung function and possibly scare some of the citizens at risk. On the other hand, too little preventive information may dilute the intervention. Thirdly, we have no spirometry measurements on the non-attendees, which complicates the comparison among the non-attendees and the attendees. Nonetheless, we have the opportunity to supply the characteristics of the non-attendees by redeemed medication and sociodemographic characteristics by the Danish registers [21, 31]. Although our population is fairly young, the most severely affected and chronic patients will not show up for the examination as it requires some physical and mental effort, but we expect the effect to be equal among the two groups. Finally, there is a risk of misclassification among, e.g., citizens with flu or pneumonia, thus resulting in false positive outcomes. However, this risk is expected to be equal among the two groups due to the randomization.

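### The design effect pairs household size with a general-practice ICC, and 1.05 does not follow from its inputs; the stated 0.90 power holds only if the household ICC is at most about 0.075 to 0.10

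*Protocol article*

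**What the plan says.** The Sample size section states: "The sample size is estimated at 4356 participants in total". The assumptions are "1:1 randomization, two-sided significance level of 0.05, power of 0.9, intra-cluster correlation coefficient of 0.01". The target is to "detect a difference of 5 percentage points in effect size based on an attendance rate of 53–58" per cent. On the inflation for clustering, the section reports that "with an average of 1.5 citizens in each household, we calculated the design effect [33] to be 1.05".

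One ICC is given, and its only justification names general practices. It was included "In order to reflect a possible clustering effect of the general practitioners", of whom there are 46, an effect "which seldom exceeds 0.01 in primary care settings".

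The Randomization section makes the household, identified by address, the unit of allocation. It adds that "the randomization is balanced at the general practitioner (GP) level"; the reason given is to spread the follow-up workload over five years.

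Under Strengths and limitations, the article explains that households were chosen as clusters to limit contamination between people who live together, because motivation to attend could affect all of them. It also says that "households are invited together and two reminders are sent out". It gives no figure for how strongly attendance is correlated within a household.

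**The concern.** A design effect needs a cluster size and an ICC from the same level, and that level must be the unit of randomisation. Here the size belongs to the household and the ICC to the general practice. Because households are allocated, a GP's citizens are divided between the arms, and similarity within a practice largely cancels from the comparison. What inflates the variance of the comparison is correlation between members of one household. The article gives a reason to expect such correlation but assigns it no value.

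Attendance is the first-listed outcome, and the Discussion says planners can use the results directly. A result near zero will be read against the stated 0.90 power for a 5-point difference, so that figure should rest on the correlation that applies.

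**Working it through.** **Inputs from the Sample size section.** Attendance 0.53 and 0.58, two-sided 0.05, power 0.90, 1:1 allocation, 1.5 citizens per household, ICC 0.01, design effect (DE) 1.05, total 4356, 46 GPs.

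**Assumed.** The household ICC, shown over a range, and the household-size distribution.

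**1. Reproduce 4356.** With pooled variance under the null and no continuity correction:

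n = [1.960 × √(2 × 0.555 × 0.445) + 1.2816 × √(0.53 × 0.47 + 0.58 × 0.42)]² / 0.05² = (1.3775 + 0.8996)² / 0.0025 ≈ 2074 per arm.

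2074 × 1.05 = 2177.7, so 2178 per arm and 4356 in total. The stated figure is reproduced exactly.

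**2. Check the design effect.** 1 + (1.5 − 1) × 0.01 = 1.005, not 1.05. With 1.005 the total would be 4170. A DE of 1.05 needs either a household ICC of 0.05/0.5 = 0.10 at size 1.5, or six citizens per household at ICC 0.01 (1 + 5 × 0.01).

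**3. Check the level.** 4356/46 ≈ 95 citizens per GP on average, allocated by household, so practices will have citizens in both arms. A GP-level design effect would be 1 + (94.7 − 1) × 0.01 ≈ 1.94, but it would apply only if GPs were randomised.

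**4. Power of 4356 under a household ICC.** DE = 1 + (k − 1) × ICC, with k = Σm²/Σm for household sizes m. At a fixed size of 1.5, k = 1.5. With half singles and half pairs, the mean is again 1.5 and k = (1 + 4)/(1 + 2) = 1.667. Power = Φ{[0.05 × √(2178/DE) − 1.3775] / 0.7019}.

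Example, ICC 0.5 at fixed size: DE 1.25, 2178/1.25 = 1742.4, square root 41.74. Then (2.0871 − 1.3775)/0.7019 = 1.011, which gives power 0.84.

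| Household ICC (assumed) | DE, fixed 1.5 | Power | N for 0.90 | DE, singles/pairs | Power | N for 0.90 |
|---|---|---|---|---|---|---|
| 0.01 | 1.005 | 0.91 | 4170 | 1.007 | 0.91 | 4176 |
| 0.1 | 1.05 | 0.90 | 4356 | 1.07 | 0.90 | 4426 |
| 0.3 | 1.15 | 0.87 | 4772 | 1.20 | 0.86 | 4978 |
| 0.5 | 1.25 | 0.84 | 5186 | 1.33 | 0.82 | 5532 |
| 0.7 | 1.35 | 0.82 | 5600 | 1.47 | 0.78 | 6084 |
| 1.0 (bound) | 1.50 | 0.77 | 6222 | 1.67 | 0.73 | 6914 |

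**5. What 1.05 covers.** 0.05/0.5 = 0.10 at fixed size, and 0.05/0.667 = 0.075 with singles and pairs.

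**The case against.** The case on the other side is that the trial is not unprotected. The 1.05 was applied to the sample size, and it absorbs a household ICC up to about 0.075 to 0.10 whatever its rationale. Clusters are small, so the loss beyond that is moderate: about 3 to 8 points over ICC 0.3 to 0.5. At fixed size, power is still 0.80 at ICC 0.8 (DE 1.40). The article says only that motivation may potentially reach the whole household, which supports some dependence but not its size. With about 3500 already enrolled when the article was submitted, a restated power changes the reporting rather than the conduct of the trial. All of this stands. It limits the size of the point but leaves the mismatch of levels and the 1.005 against 1.05 untouched.

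Three stronger readings are tempting and are not supported:

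- A reader might infer that the calculation makes no allowance for household correlation. The rationale makes none, but the number does, by accident.
- A reader might infer that the trial is underpowered. No household ICC is given, and at 0.1 the power is about 0.90.
- A reader might infer that 4356 should be inflated by the GP-level 1.94. GPs are not randomised, so it should not.

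It is equally tempting to treat 0.01 as a misprint for 0.10, which would restore 1.05. The sentence on general practitioners repeats 0.01, so the text does not support that either.

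**Conclusion.** The ICC comes from the wrong level and the design effect contradicts its own inputs. Both points follow from the Sample size and Randomization sections without any outside assumption.

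The effect on power is conditional. The stated 0.90 holds if the household ICC of attendance is no more than about 0.10, or about 0.075 with equal numbers of singles and pairs. Above that, an analysis that respects households has less: at ICC 0.5 the type II error against the trial's own 5-point target is 16 to 18% rather than 10%. These figures rest on an assumed ICC, an assumed size distribution and the 53% v 58% scenario.

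The power statement should be corrected, but this is no reason to regard the trial as unable to answer its question. A null result should be read from the precision of the estimated difference as well as from the planned power.

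**What to change.** - Replace the GP-based ICC with a household ICC of attendance, estimated from the earlier years of the same programme. Those year groups were also formed by household randomisation, and the article already reports their attendance (53% on average over 2012–2015).
- Take the household-size distribution from the same source, and use DE = 1 + (Σm²/Σm − 1) × ICC instead of the mean size alone.
- Reconcile 1.05 with its inputs: say which ICC and cluster size produced it, or correct it. Changing it to 1.005 alone would keep the wrong-level ICC and remove the accidental allowance.
- Remove GP clustering as the reason for the ICC, and restate the power of the fixed 4356 citizens over household ICCs of, for example, 0.1 to 0.7.

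The article says the SAP will be finalised before data access, so the restatement can go there. The cost is a short calculation on programme data and a slightly less favourable stated power. No extra citizens are needed and no trial procedure changes.

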### Questionnaire

Prior to the health check, the participants are asked to answer a web-based questionnaire regarding self-rated health [23], mental health [23], alcohol consumption [24], physical activity, and smoking habits using items from the Danish National Health Profile questionnaire [25]. The question concerning lung symptoms is a modified version of the question from the Clinical COPD Questionnaire [26] (Table 1). The participants are also asked which element of the preventive health check has their highest interest (not shown).

**Table 1 Tab1:** Items and response categories from the questionnaire

Do you smoke?	• Yes, daily • Yes, at least once a week • Yes, occasionally (part-time smoker) • No, I quit in (year) • No, I have never smoked
On average, how much do you smoke daily?	• Number of cigarettes • Number of cheroots • Number of cigars • Number of pipes
During the past 4 weeks, how much of the time were you troubled by dyspnea, wheezing or coughing? (only one x)	• All of the time • Most of the time • Now and then • Rarely • Not at all

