### Spirometry

Lung function will be assessed using the EasyOne Diagnostic Spirometer (Ndd Medical Technologies, Andover, MA, USA), which is calibrated daily. The spirometer measures forced expiratory volume in one second (FEV_1_) and forced vital capacity (FVC). Spirometer software calculates the FEV_1_/FVC ratio and the predicted value of FEV_1_ based on reference values. At each examination, the criterion for correct procedure performance is at least three measurements differing by less than 5%. Reversibility using a bronchodilator is not allowed. Abnormal spirometry is defined as FEV_1_/FVC <0.7 or FEV_1_% pred. <0.8 or FVC % pred. <0.8. The spirometric cut-off values used in the Global Initiative for Chronic Obstructive Lung Disease (GOLD) guidelines [27, 28] will be used for classifying disease severity.

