### Outcome

The outcomes are (1) differences in attendance rates measured by the proportion of citizens attending each of the two study groups and (2) proportion of persons at risk defined by smoking status and self-reported lung symptoms in the study groups. Furthermore, the characteristics of the two groups will be described according to sex, age, smoking history, and self-reported lung symptoms. Smoking status will be classified as smoker, ex-smoker, or never a smoker. The proportion of participants with abnormal spirometry assessed at the preventive health check will be compared between the two study groups.

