### Statistics

The effect of the intervention on attendance will be estimated by the difference of the proportion of citizens attending each of the groups. Furthermore, a descriptive analysis of attendees and non-attendees will be performed regarding sex, age, smoking history, self-reported lung symptoms, and spirometry measurements. The analysis will follow the intention-to-treat principle [16].

For the descriptive part of this study, bivariate and multivariate analyses will be performed. Numerical variables are presented as mean ± standard deviation, and binary variables as absolute numbers and relative (percent) frequencies. Student’s *t* test will be used when comparing means or changes in means of numerical variables, and Fisher’s exact *t* test or the chi-squared test will be used when comparing proportions for binary variables. Binary outcomes will be analyzed with logistic regression. The statistical significance level is set at *p* < 0.05. Statistical analysis will be performed using Stata 14.0 software [37]. A detailed Statistical Analysis Plan will be finalized before access to the data and will be attached to the ClinicalTrials.gov trial identifier (NCT02615769).

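### Dropping incomplete questionnaires and spirometry does not limit missing data; it fixes a complete-case rule for the at-risk and abnormal-spirometry comparisons beside an unqualified intention-to-treat claim

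*Protocol article*

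**What the plan says.** The rule stands in the Sample size section of the protocol article. Its stated purpose is "To limit the missing data in our study", and its content is that "incomplete questionnaires and incomplete spirometry measurements will be excluded". The article does not define incomplete, gives no denominators, and does not say which comparisons the rule governs. The same paragraph adds that non-attendees will be described from registers and that a sensitivity analysis will be done, without saying what it will examine.

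The Statistics section states, with no restriction by outcome: "The analysis will follow the intention-to-treat principle".

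The Outcome section lists three between-group comparisons:
- attendance: "differences in attendance rates measured by the proportion of citizens attending each of the two study groups";
- at-risk status: "proportion of persons at risk defined by smoking status and self-reported lung symptoms in the study groups";
- lung function: "The proportion of participants with abnormal spirometry assessed at the preventive health check will be compared between the two study groups".

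On timing, the caption of Fig. 1 places randomisation before the invitations go out. The Questionnaire section says: "Prior to the health check, the participants are asked to answer a web-based questionnaire". That questionnaire also covers self-rated health, mental health, alcohol and physical activity. The Spirometry section counts a test as correctly performed when there are "at least three measurements differing by less than 5" per cent.

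**The concern.** There are three difficulties, all of them in what the sentence states.

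1. **The rationale does not work.** Removing incomplete records leaves the missing values missing and discards the observed values that stood beside them.
2. **It sits badly with the analysis principle.** Whether a record is complete is known only after randomisation and after the citizen has read one of the two leaflets. Selecting on it is a complete-case analysis, not an intention-to-treat one. At-risk status is one of only two numbered outcomes, and the Background hypothesises that more people at risk will attend, so this is not a side analysis.
3. **It discards more than it needs to.** At-risk status requires smoking and lung-symptom answers only. A blank alcohol or physical-activity item should not cost those answers.

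At stake are some precision and, if completion depends on both arm and risk status, a distorted comparison of who was drawn in by the leaflet. The article makes such dependence conceivable: its limitations say that too much information might frighten some at-risk citizens, and that the most severely affected may stay away because the examination takes effort. It does not show that completion is affected.

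**Working it through.** **Step 1. The plan's own figure.** Inputs from the Sample size section: 53% v 58%, two-sided α = 0.05, power 0.90, 1:1 allocation, design effect 1.05. The two-proportion formula (pooled variance under the null, no continuity correction) gives 2074 per arm. Then 2074 × 1.05 = 2177.7, rounded up to 2178 per arm, or 4356 in total. This reproduces the stated N. It contains no allowance for excluded records, and attendance needs none if every randomised citizen is counted.

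**Step 2. Which data are exposed to the rule.** Expected attendees are 2178 × 0.58 ≈ 1263 and 2178 × 0.53 ≈ 1154. Only their questionnaires and spirometry can be affected.

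**Step 3. Bias in the at-risk share among attendees.** Let r be the true at-risk share, equal in both arms, c₁ the completion rate in at-risk attendees and c₀ the rate in the others. The share observed among complete records is

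r·c₁ / [r·c₁ + (1 − r)·c₀].

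The article gives none of these rates, so all of them are assumptions. Take c₁ = 0.85 in the intervention arm and 0.95 in the comparison arm, with c₀ = 0.95 in both. The comparison arm then shows r itself. The intervention arm shows:

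| r | Observed, intervention | Observed, comparison | False difference |
|---|---|---|---|
| 0.20 | 0.170 / 0.930 = 18.3% | 20.0% | −1.7 points |
| 0.30 | 0.255 / 0.920 = 27.7% | 30.0% | −2.3 points |
| 0.40 | 0.340 / 0.910 = 37.4% | 40.0% | −2.6 points |

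Swapping the arms reverses the sign (+1.7 to +2.6), so the direction is not known in advance. With at-risk completion of 80% v 90% and 95% in the others, the range is −1.8 to −2.8.

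**Step 4. When there is no bias.** If completion is 85% in all intervention attendees and 95% in all comparison attendees, c₁ = c₀ within each arm, the factor cancels, and the false difference is 0 at every r. Bias in the share among attendees therefore needs completion to depend on risk status and to do so differently by arm.

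**Step 5. The denominator matters.** The article does not state one for this outcome. If it were at-risk attendees per invited citizen, a difference by arm alone would be enough. With 53% attendance and r = 0.30 in both arms, the true value is 0.53 × 0.30 = 15.9%. Completion of 90% v 95% gives 0.159 × 0.90 = 14.3% and 0.159 × 0.95 = 15.1%, a false difference of about 0.8 points.

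**Step 6. Precision.** With 90% of records complete in both arms (assumed), standard errors for a share among attendees grow by 1/√0.90 = 1.05, about 5%. Part of this is recoverable, because some incomplete questionnaires will still hold the smoking and symptom answers.

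The formula in Step 3 applies in the same way to abnormal spirometry, with r as the share who are abnormal.

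**The case against.** A reader might infer more: that attendees with incomplete records leave the trial altogether, so that the attendance comparison itself is biased and intention to treat is contradicted for the outcome that sizes the trial. The document does not support this. The sentence excludes questionnaires and measurements, not citizens. Attendance needs neither. Under a person-level rule every non-attendee would also have to go, since they have no spirometry, and attendance would be near 100% in both arms; yet the next sentence keeps non-attendees and describes them from registers. Calculations that recount attendance among complete attendees only therefore do not apply.

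The other side has further good arguments.
- Arm-dependent completion is a possibility without evidence. For spirometry it is made less likely by the blinding of health professionals stated under Randomization and by the monitored standard procedure described under The health check.
- Both affected comparisons are seen only in attendees, a selection that exists whatever is done with incomplete records.
- Setting aside measurements that fail a quality criterion is ordinary practice.
- A sensitivity analysis is promised, and a detailed SAP is to follow before data access; methods for missing data are commonly left to it.

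All of this stands and limits the size of the point. It does not remove it. The article has not left the handling of incomplete records open; it has stated a rule, given a reason that the rule does not serve, and placed it beside an intention-to-treat statement with no stated exception. The sensitivity analysis has no stated target, so it cannot be taken to cover this.

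**Conclusion.** The point holds for the at-risk outcome and the abnormal-spirometry comparison, and only there. The rule is a complete-case rule on data collected after randomisation and after the leaflet, its rationale is mistaken, and it discards usable smoking and symptom answers. The certain cost is some lost precision. Bias is possible, not shown: about −1.7 to −2.6 points in the at-risk share under the assumed 20–40% at risk and 85% v 95% at-risk completion, of either sign, and zero for the share among attendees if completion differs by arm only. Attendance, its intention-to-treat analysis and N = 4356 are unaffected on the natural reading. This is a cheap improvement to a stated rule, not a threat to the trial's main result.

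**What to change.** Replace the exclusion sentence with a statement that:

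(a) attendance is analysed in all randomised citizens, whatever the state of their questionnaire or spirometry;

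(b) at-risk status uses the smoking and lung-symptom items wherever they are answered, not only from fully complete questionnaires, with the denominator stated;

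(c) attendees with failed or incomplete spirometry are kept as a separate category and reported by arm;

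(d) the sensitivity analysis already promised addresses this missingness, for example by multiple imputation among attendees or by best-case and worst-case counting.

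The wording can go into the SAP that the Statistics section promises before data access. The cost is one rewritten sentence, denominators that vary slightly between comparisons, and a small amount of extra analysis. The sample size and data collection do not change.
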